### 3. STUDY DESIGN

An RCT with a cost-effectiveness analysis, will be performed in three non-university large teaching hospitals in the Netherlands (Amphia Hospital Breda, Elisabeth Tweesteden Hospital Tilburg and Meander Medical Center Amersfoort), during the period of November 2025 to May 2028. All patients of 65 years or older, with a new onset of CLTI presented at the outpatient clinic of the vascular surgeon, who are planned for surgical or endovascular revascularization and who meet the in- and exclusion criteria are asked to participate in the study. In addition, their primary IC will also be requested to take part in the study. A primary IC is defined as follows: the person most involved in caring for the CLTI patient and supporting at least one instrumental activity of daily living of the patient or defined as the contact who supports in decisions by the patient. Patients can still be included, if their primary IC refuses participation. However, primary ICs can only be included together with a patient.

At the outpatient clinic information about the POCI-study is provided by a VNP or researcher and patients and ICs receive an information folder. They are called by telephone the next day by a researcher or VNP to ask if they want to participate. If so, oral informed consent will be obtained by the researcher or VNP and patients are randomized immediately upon inclusion, either into the prehabilitation group or the control group, the latter receiving the standard of care. Their IC will automatically be randomized to the same group. Within a few days all patients undergo a general health screening by a VNP or researcher and a blood sample will be taken as part of the standard care. Written informed consent will be obtained during this visit. Afterwards patients receive three questionnaires: the WHOQoL-BREF, the EQ-5D-5L and the iMTA Medical Consumption Questionnaire (iMCQ) (t=0). ICs are also asked to fill in two questionnaires: the WHOQoL-BREF, and the CSI (t=0). Afterwards, patients randomized into the intervention group are referred to the prehabilitation program where they are assessed by a physiotherapist and if indicated also a geriatrician, dietician or a quit smoking coach. The prehabilitation program will take two weeks, considering both the time needed to possibly reach significant results with the program and the time in which treatment is planned and must take place.

After treatment planning is complete, the vascular surgeon will discuss this plan with patients and their IC in a second visit to the outpatient clinic. Afterwards both patient and IC are asked to fill in three questionnaires, regarding the SDM process: the CollaboRATE, the ACPS and the PICS (tSDM=0).

Patients and their ICs will be included during a period of 2 years and will stay in follow-up for 6 months. At the 6-months follow-up patients are asked to fill in four questionnaires: the

WHOQoL-BREF, the EQ-5D-5L, the iMCQ and a process evaluation form designed by the researchers (t=1). ICs are asked to fill in three questionnaires: the WHOQoL-BREF, the CSI and a process evaluation form (t=1).

Inclusion of the patient and their IC will be on the day after the first outpatient clinic visit. This way the prehabilitation starts within a few days, parallel to the treatment planning (imaging, multidisciplinary meeting, planning for surgery or endovascular treatment) and there will be no delay in the treatment schedule.

FIGURE 1 – FLOWCHART POCI-STUDY

[figure not shown]

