## SUMMARY

**Rationale:** Chronic limb-threatening ischemia (CLTI) is the most severe form of peripheral arterial disease (PAD). CLTI primarily occurs in older adults and is associated with the need for (multiple) hospital admissions and significantly reduces the quality of life (QoL). Despite the increase of (more expensive) minimally invasive techniques (endovascular procedures) and surgeries, the associated complications, the risk of mortality, reduction in QoL, and decline in daily functioning remain high.

**Objective:** The aim of this study is to minimize the length of hospital stay (LOS) and improve patients' (clinical) outcomes, particularly their QoL, through prehabilitation prior to a CLTI intervention. Additionally, we aim to reduce healthcare costs and to improve the process of shared decision making (SDM).

**Study design:** This is a randomized multicentre study, with a cost-effectiveness analysis.

**Study population:** All CLTI patients aged 65 years or older presenting to the vascular surgeon with a new onset of CLTI who are planned for surgical or endovascular revascularization are screened for eligibility. Their primary IC will also be asked to participate in the study.

**Intervention (if applicable):** All patients undergo a general health screening by a vascular nurse practitioner (VNP) or researcher at the Multidisciplinary Vascular surgical outpatient clinic for the Elderly (MVE). Afterwards patients randomized to the intervention group are offered a prehabilitation program, starting directly at the MVE. Patients are referred to a physiotherapist and if indicated also to a geriatrician, dietician and a quit smoking coach. All will collaborate to optimize the patient's preoperative condition, to shorten the LOS and improve QoL of both patient and IC. In summary the prehabilitation program consists of: physical training, lifestyle advice, diet advice and supplements, iron infusion (Ferinject) in case of an iron deficiency anaemia and a comprehensive geriatric assessment (CGA).

**Main study parameters/endpoints:** The primary outcome is the LOS. Secondary outcomes will be QoL of the patient and their IC, 6-month mortality, postoperative complications, hospital readmission, 2level of perceived SDM and preferred participation in SDM of the patient and their IC, perceived and preferred roles in decision making (DM) of the patient and their IC and cost-effectiveness.

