#### Multidisciplinary Vascular surgical outpatient clinic for the Elderly (MVE)

Directly after inclusion patients will be referred to the MVE. It is important that the patient brings an informal caregiver, for example a partner, family member or close friend to optimize the (hetero)anamnesis and to make sure all information is understood and processed well. Also, hereby we can investigate the possibility of informal care, provided by friends or family. If needed, home care will already be arranged for after discharge. Written informed consent for participating in the study will be obtained by a researcher or VNP.

- *Vascular surgery Nurse Practitioner or researcher*

A trained VNP or researcher will screen all patients on baseline characteristics, signs of frailty and the presence of risk factors for delirium. Comorbidity will be scored using the V-POSSUM score, ASA-classification, Charlson comorbidity index and the Comprehensive Comorbidity Index (CCI) (Appendix 2-Meetinstrumenten). Frailty will be scored using the Clinical Frailty Scale (CFS) (13) and the Geriatric-8-score (G8-score) (14). The VNP or researcher will withdraw the Mini Mental Status Exam (MMSE) (15) to assess cognitive function. Dietary state is assessed by using the Short Nutritional Assessment Questionnaire (SNAQ-score) (16). Also, an inventory is made of available (informal) care and whether problems are expected after dismissal. Patients randomized to the intervention group, might subsequently be referred to the geriatrician, dietician and a 'quit smoking coach' if necessary.

- *Biochemistry tests*

Biochemistry tests will be performed prior to the visit to the VNP or researcher at the MVE. This will consist of: haemoglobin, haematocrit, MCV, C-Reactive Protein, leukocytes, thrombocytes, liver enzymes (ASAT, ALAT), electrolytes (sodium, potassium, chloride), albumin, MDRD, urea, creatinine, INR, lipid spectrum including cholesterol, vitamin D, vitamin B12, folium acid, transferrin, ferritin. Therefore, three blood tubes will be taken.

- *Physiotherapist*

After the visit to the VNP or researcher, patients in the intervention group will be screened by a physiotherapist. The physical state of the patient will be examined and the following tests are performed:

- Maximal inspiratory and pressure (MIP);
- The 'De Morton Mobility Index' (DEMMI)
- Gripstrength, using the hand dynamometer (JAMAR®);
- Timed Up and Go (TUG) test;
- Timed Chair-Stand test;

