### 11.2 Recruitment and consent

Patients and their IC will be asked to give written informed consent while visiting the MVE by the VNP or a researcher. The patient information letter, the informal caregiver information letter and the informed consent forms for patients and their IC are attached (E1.Proefpersonen informatiebrief and E.1Mantelzorger informatiebrief).

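### Randomisation precedes written consent, health screening and the t=0 questionnaires, so baseline QoL, caregiver strain and utility can be coloured by knowledge of the arm, and patients can decline to sign after allocation

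*Protocol*

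**What the plan says.** Protocol Section 3 fixes the order of events. Study information is given at the first outpatient visit. Then: "They are called by telephone the next day by a researcher or VNP to ask if they want to participate". On agreement, "oral informed consent will be obtained by the researcher or VNP and patients are randomized immediately upon inclusion". The caregiver (IC) takes the patient's arm. Next: "Within a few days all patients undergo a general health screening by a VNP or researcher". About that visit the protocol says: "Written informed consent will be obtained during this visit. Afterwards patients receive three questionnaires", namely the WHOQoL-BREF, EQ-5D-5L and iMCQ. The IC receives the WHOQoL-BREF and CSI at the same time point.

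Other sections agree with this order. Section 11.2: "Patients and their IC will be asked to give written informed consent while visiting the MVE by the VNP or a researcher". Section 8.2 has the VNP or responsible researcher randomise immediately after inclusion and states that there is no blinding. Section 8.3 gives the screening to the same roles: "A trained VNP or researcher will screen all patients on baseline characteristics, signs of frailty and the presence of risk factors for delirium". The Summary places the start of the intervention after that screening: "Afterwards patients randomized to the intervention group are offered a prehabilitation program, starting directly at the MVE".

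Sections 10 and 10.2 use baseline characteristics as covariates, and Section 10.2 calculates QALYs from the EQ-5D at 0 and 6 months.

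**The concern.** A baseline measure should be fixed before anyone can know the arm. Here every t=0 questionnaire and every staff-scored screening item comes after allocation in an open-label trial. A patient or IC who knows whether the program is coming may rate quality of life or strain differently. A rater who knows the arm may score frailty or comorbidity differently. If t=0 differs by arm for that reason, any comparison that uses t=0 inherits the difference: a change score, a baseline-adjusted contrast, or an area-under-the-curve QALY. Section 8.2 relies on objective outcomes and standardised assessment to limit bias, which does not reach self-reported forms.

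The order also opens a gap between allocation and signature. Someone who agreed orally can decline to sign after allocation, and the reasons may differ by arm. Sections 8.4 and 8.6 keep clinical data after withdrawal, and Section 10 prescribes intention to treat. No section says whether these rules cover a patient who never gave written consent; Section 11.1 speaks of withdrawal after written consent. Section 8.5 allows no replacement.

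**Working it through.** **1. Order of events (Section 3, checked against 8.2, 8.3 and 11.2).** First visit and information; telephone call next day; oral consent; randomisation; a few days later the screening visit with written consent; then the t=0 forms. The sections agree, so this is the intended design and not a slip in one place.

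**2. Effect on the QALY (assumed shift; the documents give none).** With two utilities u0 and u6 over 0.5 year, the trapezoid is

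QALY = 0.5 × (u0 + u6)/2 = 0.25·u0 + 0.25·u6.

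An upward shift s in u0 in one arm, with no true effect, moves that arm's unadjusted QALY by +0.25·s:
- s = 0.02: +0.005
- s = 0.05: +0.0125
- s = 0.10: +0.025

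**3. Effect on a six-month comparison (same shift; assumed slope of six-month on t=0 utility = 0.5).** Baseline adjustment subtracts slope × shift, so that arm's adjusted difference moves by -0.5·s:
- s = 0.02: -0.01
- s = 0.10: -0.05

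A comparison of change from t=0 subtracts the whole shift, so it moves by -0.02 to -0.10. Section 10.2 does not list the baseline score among its covariates and names mixed models for repeated measures, so which of these applies is open. The sign differs between steps 2 and 3: the same t=0 shift flatters the arm on the unadjusted QALY and penalises it on the adjusted six-month score.

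**4. Length of stay through late refusal.** The plan's own figure first (Section 4.4: 150 per arm, SD of log LOS 0.9, ratio 0.75, two-sided 5%):

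SE = 0.9 × √(2/150) = 0.1039; |ln 0.75|/SE = 0.2877/0.1039 = 2.77; power = Φ(2.77 - 1.96) = 79.1%, which matches the stated 80%.

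The following holds only if late refusers leave the analysis; the rates are assumptions.
- Equal loss of 5/10/15/20% in both arms: power 77.0/74.7/72.3/69.7%.
- Loss of a fraction l in the intervention arm only, where those lost have mean log LOS 0.5 SD above their arm's mean: bias = -l/(1 - l) × 0.5 × 0.9. For l = 0.10 this is -0.05, so a true ratio of 1.00 appears as exp(-0.05) = 0.95, with two-sided type I error about 7.5%. For l = 0.05 to 0.20 the apparent ratio is 0.98 to 0.89 and the type I error about 5.6% to 18%.

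If they are retained under intention to treat, none of step 4 arises.

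**The case against.** The stated reason for early inclusion is sound: Section 3 wants prehabilitation to run in parallel with treatment planning and cause no delay. Section 3 also says only that patients receive the questionnaires, so requiring completion before allocation could cost time if the forms went home. That stands as a constraint on the remedy, and it is why completion must be on site.

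Several stronger readings are tempting and do not hold.

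- A reader might infer that t=0 values are certainly distorted because patients hear their arm during the call. No section says when the patient or IC is told. Open-label randomisation by staff who may have made the call makes early knowledge likely, but only the possibility is established.
- A reader might infer that the cognitive exclusion is tested only after allocation, through the MMSE at the screening visit. Section 4.3 excludes people unable to complete questionnaires and names no MMSE criterion. Section 4.1 screens eligibility before the study is offered. The stated MMSE threshold, in Section 8.3, triggers geriatric referral.
- A reader might infer that each unsigned patient is lost to the trial. Sections 8.4, 8.6 and 10 point towards retention; the defect is that they do not say whether they reach this case.
- A reader might infer that the length-of-stay model is compromised through its covariates. Those listed in Section 10.1 are mostly demographic or history facts that predate allocation, and LOS is extracted from the electronic record.

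The exclusion in Section 8.4.1 of patients who refuse the program sits badly with intention to treat. That is a separate matter: such refusals come after allocation whatever the timing of randomisation.

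**Conclusion.** The point holds as a should-fix. As written, the order of events lets knowledge of allocation reach self-reported and rater-scored baseline values, and it lets patients decline written consent after allocation without a stated rule for their data.

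The comparisons at risk are secondary: QoL of patient and IC, caregiver strain, and QALYs. Under the assumed t=0 utility shift of 0.02 to 0.10, the effect is +0.005 to +0.025 on the unadjusted six-month QALY, or -0.01 to -0.05 on a baseline-adjusted six-month utility at slope 0.5. These sizes rest on assumptions; the documents supply neither shift nor slope. Age, sex and blood values are hardly affected. The primary endpoint is exposed only through late refusal, and only if those patients are dropped. The sample size and its power are unchanged by the correction.

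**What to change.** Amend Sections 3, 8.2 and 8.3 so that the telephone call records oral agreement and books the screening visit, without randomising. At that visit, in this order: written consent; screening by the VNP or researcher; on-site completion of the t=0 questionnaires by the patient, and by the IC if participating. Only then generate and disclose the allocation in Castor EDC, and refer the intervention arm to the program directly, as now. Section 5 already sends all patients through this visit, and the program starts only there, so the parallel timetable can be kept if the forms are completed on site. Anyone who declines to sign is then never randomised, and the question of their data falls away.

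For any patients randomised under the present order, state whether those who gave only oral consent are covered by the data-retention and intention-to-treat rules, and report losses before signature by arm.

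Cost: a protocol amendment, time and space for on-site completion, and physiotherapy slots held provisionally before the arm is known, about half of which would go unused with equal allocation.

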## 4. STUDY POPULATION

### 4.1 Population (base)

All patients in the Amphia Hospital (Breda), the Elisabeth Tweesteden Hospital (Tilburg) and the Meander Medical center (Amersfoort), referred by a general practitioner with suspected CLTI, will be seen on the outpatient clinic by a vascular surgeon. Diagnosis of CLTI is based on impaired perfusion combined with a Rutherford classification of either stage 4 or 5 (8). The severity of the CLTI is scored by the vascular surgeon by using the Wifl score (9). All CLTI patients exceeding the age of 65 with a Wifl-score of Wounds (W)  $\leq 2$  and foot infections (fi)  $\leq 2$  are screened for eligibility according to the in- and exclusion criteria stated below. Additional imaging is requested. If eligible, patients are offered the study information and asked to participate in this study. Their primary IC will be asked to participate with the patient.

### 4.2 Inclusion criteria

In order to be eligible to participate as a patient in this study, a participant must meet all of the following criteria:

- Aged 65 years or older
  - Diagnosis of CLTI (Chronic Limb Threatening Ischemia), based on:
    - Anamnestic complaints of ischemic rest pain or night pain (Rutherford stage 4) OR (Minor) tissue loss, non-healing ulcer and/or focal gangrene with diffuse pedal ischemia (Rutherford stage 5) (8)
- AND

Impaired perfusion, quantified by a flat or barely pulsatile ankle or metatarsal pulse volume recording (PVR), a low resting ankle pressure, a low ankle brachial index and/or a low toe pressure.

In order to be eligible to participate as an IC in this study, a participant must meet the following criterium:

- IC of a CLTI patient of 65 years or older

### 4.3 Exclusion criteria

A potential participant who meets any of the following criteria will be excluded from participation in this study:

- Patients undergoing conservative therapy
- Need for urgent surgery or endovascular therapy (<2 weeks), based on either:
  - Wifl-score of W = 3
  - Wifl-score of fi = 3
- Patients or ICs who are unable to complete questionnaires, due to either lingual or cognitive incompetence.

#### 4.4 Sample size calculation

In this multicenter study we aim for a total of 300 patients, 100 patients from each hospital. With this sample size we have 80% statistical power to test hypotheses with 2-sided alpha set at 5% for the following differences between randomized groups.

Length of hospital stay: The calculation of the effect size is based on the difference in means with SD. In a previous study (7), prehabilitation was associated with a difference of 2 vs over 4 days on average. A halving in length of stay requires 54 patients in total (27 per group, assuming a SD of log (LOS) of 0.9, as in the previous study). With 300 patients, a decrease by a factor 0.75 (so 25% reduction in LOS) provides 80% power.

For complications, we will analyze minor and major complications. In the previous study (7), prehabilitation was associated with the following reductions in complications: minor, 26 vs 14%; major 23 vs 18%. These differences would require sample sizes of 346 and over 2000 patients in total respectively. With 300 patients we will have reasonable power for detecting a difference in minor complications (power 69%), but insufficient statistical power for a difference of 23 vs 18% in major complications (power 15%). These calculations were done using the online sample size calculators at <https://sample-size.net/>

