## 10. STATISTICAL ANALYSIS

Statistical analyses are performed using IBM SPSS statistical software (SPSS Inc., Chicago, Illinois, USA). A two-sided p-value of less than 0.05 will be considered statistically significant. Adjusted analysis with prognostic baseline characteristics (e.g. gender, age) will be performed using regression analysis. This analysis corrects for baseline differences, optimizes statistical power, and provides better individualized treatment effect estimates. Missing data will be studied for specific patterns of occurrence, and multiply imputed. A power analysis with sample size calculation is performed, as described in paragraph 4.4 (sample size calculation).

Results of categorical data variables are described in frequencies with percentages and differences will be tested using the Chi-square test. Continuous data are described as median (interquartile range) and Mann-Whitney U-tests will be performed to test for group differences. Ordinal variables will be tested using the Mann-Whitney U-test. Data analysis will be done according to the intention-to-treat concept, which implies that all patients are included in the analysis irrespective of whether they completed the prehabilitation program. Secondary, a per protocol analysis will be performed, although interpretability may be difficult for this analysis. All epidemiological issues and statistical methods will be discussed with [name]. [name], a member of the research group.

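### Section 4.4: the 346 patients required for minor complications and the 69% power at 300 patients rest on different calculation bases

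*Protocol*

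**What the plan says.** Protocol section 4.4 sets the size of the trial: "we aim for a total of 300 patients, 100 patients from each hospital". It introduces the calculations with a general claim: "With this sample size we have 80% statistical power to test hypotheses with 2-sided alpha set at 5% for the following differences" between the randomised groups. Length of stay comes first, with 80% power attached to a 25% reduction.

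Complications follow. Rates of 26% versus 14% (minor) and 23% versus 18% (major) are taken from a previous study, and the section says: "These differences would require sample sizes of 346 and over 2000 patients in total respectively". It then turns to the planned size: "With 300 patients we will have reasonable power for detecting a difference in minor complications (power 69"%). For major complications it gives 15% and calls that insufficient. All these calculations are credited to one online calculator site. No continuity correction is mentioned, and no change of method between the sample sizes and the powers.

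On analysis, Protocol section 10 says of categorical data that "differences will be tested using the Chi-square test". Section 10.2 plans covariate-adjusted logistic regression, with hospital site as a factor, for binary secondary outcomes.

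**The concern.** A required sample size and a power at another sample size, computed from the same rates, alpha and test, are two points on one curve. If 346 patients give 80% power, the power at 300 is fixed. A fall from 80% to 69% is too steep for a cut from 346 to 300, which suggests that the two figures come from different formulas.

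The general 80% claim at the head of the section also cannot cover the complication outcomes, because the section itself puts them at 69% and 15%.

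What is at stake is modest. Complications are the only secondary outcome with a power statement. A reader who tries to reproduce 346 and 69% together will fail, and may then doubt the length-of-stay calculation, which is sound.

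**Working it through.** **Inputs (Protocol section 4.4).** Two-sided alpha 0.05 (z = 1.960); target power 80% (z = 0.842); total 300; rates 0.26 vs 0.14 and 0.23 vs 0.18. Allocation is taken as 1:1, so 150 per arm. The ratio is not stated in words, but the length-of-stay calculation uses equal groups ("A halving in length of stay requires 54 patients in total (27 per group") and section 8.2 uses blocks to avoid unequal groups.

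**Formulas.** With d = p1 − p2 and p̄ the mean of the two rates:

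- Uncorrected size per arm: n = [1.960·√(2p̄(1−p̄)) + 0.842·√(p1(1−p1) + p2(1−p2))]² / d²
- Continuity-corrected size per arm: n_c = (n/4)·[1 + √(1 + 4/(n·d))]²
- Power at m per arm: Φ[(d − c − 1.960·SE0)/SE1], with SE0 = √(2p̄(1−p̄)/m), SE1 = √((p1(1−p1) + p2(1−p2))/m), and c = 0 (uncorrected) or c = 1/m (corrected)

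**Step 1: reproduce 346 (minor).** 2p̄(1−p̄) = 0.32 and p1(1−p1) + p2(1−p2) = 0.1924 + 0.1204 = 0.3128.

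- Uncorrected: n = (1.960·0.5657 + 0.842·0.5593)² / 0.0144 = 173.2 per arm. Doubled, this is 346; with each arm rounded up it is 348.
- Corrected: n_c = (173.2/4)·[1 + √(1 + 4/20.79)]² = 189.5 per arm, so 190 per arm and 380 in total.

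The stated 346 is therefore the uncorrected size.

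**Step 2: reproduce 69% (minor, 150 per arm).** SE0 = 0.04619, SE1 = 0.04567.

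- Uncorrected: Φ[(0.12 − 0.09053)/0.04567] = Φ(0.645) = 74.1%.
- Corrected: Φ[(0.12 − 0.00667 − 0.09053)/0.04567] = Φ(0.499) = 69.1%.

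The stated 69% is the corrected power.

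**Step 3: reproduce 15% (major, 150 per arm).** 2p̄(1−p̄) = 0.32595 and 0.1771 + 0.1476 = 0.3247, so SE0 = 0.04662 and SE1 = 0.04653.

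- Uncorrected: Φ[(0.05 − 0.09136)/0.04653] = Φ(−0.889) = 18.7%.
- Corrected: Φ[(0.05 − 0.00667 − 0.09136)/0.04653] = Φ(−1.032) = 15.1%.

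The stated 15% is also the corrected power. The required totals are 2,046 uncorrected and 2,124 corrected.

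**Step 4: other explanations.**

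| Method, 150 per arm | Minor | Major |
|---|---|---|
| Stated in section 4.4 | 69% | 15% |
| Uncorrected, pooled | 74.1% | 18.7% |
| Uncorrected, unpooled | 74.8% | 18.8% |
| Arcsine | 74.7% | 18.8% |
| Chi-square, exact enumeration | 74.7% | 18.9% |
| Continuity-corrected | 69.1% | 15.1% |
| Yates chi-square, exact enumeration | 69.7% | 15.3% |
| Fisher, exact enumeration | 69.7% | 15.3% |
| One-sided, uncorrected | 83.3% | 28.3% |

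Neither the choice of variance nor sidedness explains the gap. Only the corrected calculation and its near-equivalents do.

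**Step 5: cross-check at 346 (minor).** With 173 per arm, power is 79.9% uncorrected and 75.9% corrected. So 346 at 80% and 300 at 69% do not lie on one curve.

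**The case against.** The strongest reply is that nothing depends on this. The stated powers err on the low side, minor complications fall short of 80% on either basis, and major complications are underpowered on either basis. Section 4.4 ties 300 patients to length of stay. All of that stands, and it is why the point is minor.

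Four stronger readings are tempting, and the protocol does not support them.

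- **That the total for major complications is also wrong.** The text says only over 2,000, and both 2,046 and 2,124 satisfy that. The one proven clash between a sample size and a power is 346 against 69%.
- **That 69% and 15% are wrong for the planned test.** Section 10 names a Chi-square test without saying whether it is corrected, and section 10.2 plans adjusted logistic regression, which neither basis describes exactly. The uncorrected basis is the more natural reading of section 10, but the protocol does not prescribe it.
- **That a continuity correction was certainly used.** It is inferred from close agreement on two figures. A Yates or Fisher calculation comes nearly as close.
- **That the 80% for length of stay is also an error.** With a log-scale SD of 0.9 and a ratio of 0.75, power at 150 per arm is Φ[0.2877/(0.9·√(2/150)) − 1.960] = 79.1%. That is ordinary rounding, and 54 patients for a halving reproduces.

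It can also be said that the opening 80% sentence misleads few readers, since the lower figures follow within the same short section. That is fair, but the sentence is still untrue as worded.

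**Conclusion.** The point holds in a limited form. For minor complications, 346 is an uncorrected size and 69% a corrected power, so the two cannot stand side by side. The 15% for major complications is on the corrected basis too. Put on the basis that yields 346, the powers at 300 are 74% and 19%, so the stated values are about 5 and 4 points low. Put on the basis that yields 69%, the required total rises from 346 to 380. The opening 80% claim is contradicted within its own section.

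This rests on 1:1 allocation, 300 patients analysed, and unadjusted comparison of two proportions at the protocol's rates. A reader might infer that the trial is mis-sized or that its main claim is unsound. It is not: the primary outcome carries the sample size, and that calculation reproduces. Nor does the protocol rank complications above its other secondary outcomes. Severity is minor.

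**What to change.** In Protocol section 4.4, choose one basis, name it, and use it for both the sample sizes and the powers.

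- **Preferred, uncorrected:** required total 346 (348 if each arm is rounded up); power at 300 analysed 74% for minor and 19% for major complications. This sits best with section 10, which names a Chi-square test and no correction.
- **Equally consistent, corrected:** keep 69% and 15%, state that a continuity correction was applied, and change 346 to 380.

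The phrase giving over 2,000 for major complications can stay in either case. Reword the opening sentence so that 80% power refers only to the 25% reduction in length of stay.

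The cost is one or two figures, a few words naming the method, and one sentence. The design, the target of 300 and the planned analysis do not change.
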